**Table 1 Tab1:** **Schedule of the four subgroups in the TELEGRAFT study**

	High-risk (KTFS > 4.17)		Low-risk (KTFS ≤ 4.17)	
	Standard	eHealth	Standard	eHealth
Day 0 (inclusion)	CC and data collection (written consent, QoL)			
Week 03	-	VC	-	-
Week 06	SV	SV	-	-
Week 09 (Month 2)	-	VC	SV	VC
Week 12 (Month 3)	SV	SV	-	-
Week 15	-	VC	-	-
Week 18 (Month 4)	SV	SV	SV	VC
Week 21	-	VC	-	-
Week 24 (Month 6)	SV	SV	SV	VC
Week 27	-	VC	-	-
Week 30	SV	SV	-	-
Week 33	-	VC	-	-
Week 36	SV	SV	-	-
Week 39	-	VC	-	-
Week 42	SV	SV	-	-
Week 45	-	VC	-	-
Week 48	SV	SV	-	-
Week 50	-	VC	-	-
Week 52 (Month 12)	CC and data collection (pathology, QoL, morphologic exams)			
Month 13	-	VC	-	-
Month 14	SV	SV	-	-
Month 15	-	VC	SV	VC
Month 16	SV	SV	-	-
Month 17	-	VC	-	-
Month 18	SV	SV	SV	VC
Month 19	-	VC	-	-
Month 20	SV	SV	-	-
Month 21	-	VC	SV	VC
Month 22	SV	SV	-	-
Month 23	-	VC	-	-
Month 24	CC and data collection (laboratory works, QoL, morphologic screaming)			

SV, Standard Visit at hospital; CC, Complete Check-up at hospital; VC, Video Conferencing at home; Qol, Quality of Life.

### Calculation of kidney transplant failure score

The KTFS calculation is facilitated by an application available on smartphones, tablets, or computers at http://www.divat.fr/en/online-calculators. The reportable results are exported as a simple file in Portable Document Format (PDF), and contains the results in terms of patient classification and risk of return to dialysis.

### Outcome measures

The primary outcome is composite and defined by the absence of major complications until two years post-randomization, i.e. a patient is alive with a functional kidney, without acute rejection episodes, without a decrease in the graft filtration rate (eGFR) higher than 25% estimated by the Levey’s formula [7] and without cancer. Other secondary outcomes will also be analyzed to evaluate the efficiency of the eHealth program: 1) The incremental cost-effectiveness ratios (ICER) comparing eHealth with at-hospital follow-up programs, estimated from the perspective of the health care system as the mean difference in two years costs divided by the mean difference in Quality-Adjusted Life Years (QALYs) calculated using the EuroQol EQ-5D questionnaire [8]. One ICER will be estimated for both the low and high risk patient groups. 2). The evolution of the transplant-specific or generic QoL respectively measured by the ReTransQoL and the SF36 questionnaires [9–11]. 3) The evolution of other psychological dimensions related to the stress by using the ways of coping checklist [12], the anxiety/depression by using the hospital anxiety and depression scale [13] and by using the post-traumatic growth inventory [14].

All outcomes will be compared between patients allocated to the eHealth program versus those in the control standard care group. Secondarily, the same comparisons will also be performed within each subgroup of graft failure susceptibility, i.e. KTFS +/- 4.17.

### Sample size

We initially aimed to include a total of 700 patients, which was based on the number of participating centers and the workload of each center. Unfortunately, due to technical difficulties in video conferencing, we will recruit a total of ~250 transplant recipients. Assuming 90% of patients without complication in both groups for the primary outcome, a one-sided type I error level of 0.05 and a 3% non-inferiority margin, this sample size of 125 patients in each group is associated with a power at 20%. Therefore, we acknowledge that the statistical power of the TELEGRAFT study is low. 1,237 patients per group would have been necessary to reach a power of 80%. Nevertheless, a total sample size of 2,474 recipients is obviously impossible to obtain, since it represents approximately the total number of kidney transplantations for one year in France.

### Data acquisition

Demographic, clinical variables, and other specific questionnaires are collected in the DIVAT (Données Informatisées et VAlidées en Transplantation) multicentric and prospective cohort using *Integralis®,* a web-based application for data management of observational cohorts (http://www.idbc.fr)*.* The data related to the specific questionnaires are manually completed by the patients, and subsequently entered in the data base.

### Data analysis

A first descriptive analysis of the patients’ characteristics between both groups will be conducted to identify possible confounding factors, even though randomization should ensure comparability. The eHealth program versus the standard of care will be concluded as non-inferior if the lower limit of the 90% confidence interval (CI) of the difference in the primary endpoint (percentage of patients without major complications), calculated by non-parametric bootstrapping, is higher than -3%. For secondary outcomes, two-sided 95% CIs will be computed and two-tailed t-tests or chi-square statistics will be used to report p-values. 95% confidence intervals for ICER of eHealth versus at-hospital follow-up programs will be estimated using non-parametric bootstrapping. Results of the cost-effectiveness will also be analyzed using acceptability curves, by plotting the probability of eHealth program compared to standard of care follow up being cost-effective against the willingness to pay for a QALY. Deterministic sensitivity analyses will also be performed to assess the robustness of results depending on the cost of the video conferencing system. The evolution over time of each psychological dimension will be modeled using latent mixed regression Rasch models [15]. These models allow the responses to the items of each dimension to be transformed in a quantitative measure that represents the concept studied by this dimension, and allows measures to be explained by covariates. These models take into account the repeatability of the measures for each patient by using a random effect. For the dimensions where the Rasch model will not fit the data, the score computed as the sum of the items of this dimension will be modeled using a mixed linear model. With these models, the effect of the eHealth program on the evolution of the psychological measures will be determined, and this effect will be adjusted on other covariates (sex, age, risk classification…).

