In the present study, we hypothesize that the efficiency of the kidney transplant recipient follow-up after one year post-transplantation could be further improved by adapting it to the risk of graft failure defined by the KTFS estimation. We propose video conferencing in addition to the KTFS estimation at one-year in order to 1) decrease the number of visits at hospital for low-risk patients without reduction in quality of life or graft survival and 2) increase the number of visits for high-risk patients with a possible improvement in graft survival.

The primary aim of the study is to evaluate the efficiency of a personalized follow-up for kidney transplant recipients that consists of adapting the frequencies of video conferencing at home and visits at hospital depending on the KTFS value. We expect such a personalized follow-up to be cost-effective compared to the conventional in-hospital follow-up strategy for both low- and high-risk patients groups.

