## Discussion

The cost-effectiveness of renal transplantation for ESRD patients is well-established compared to long-term dialysis [16–18]. Nevertheless, because the follow-up of the kidney transplant recipient is often performed at hospitals several times per year, is often coupled with significant travel requirements, long queue times and the stress associated with medical examinations, this places a measureable increase in costs and may impact the recipient’s QoL. This issue is even more pertinent when considering the increased prevalence of patients living with a functional kidney; 31,000 French patients in 2011 [1]. We hypothesized that video conferencing at home by using USB device and tablet computer may improve the efficiency of kidney transplant recipient follow-up. Such web- or mobile-based communication systems have already been considered as possible improvements for medical follow-up for other diseases; for instance in diabetes patients [19], in women after gynecological surgery [20], or for patients with chronic obstructive pulmonary disease [21].

One very important and relevant potential benefit of our adaptation of the video conferencing frequency is in regard to the frailty of patients, i.e. their risk of graft failure evaluated by the KTFS [6]. The aim of the TELEGRAFT study is to determine whether video conferencing could be used to individualize patients’ care so as to lighten (reinforce) follow-up in low (high) risk patients as compared to standard of care at hospital. This reallocation of health care resources could be profitable in many aspects. On one hand, it might increase the QoL of low-risk patients by offering them living conditions closer to those of the general healthy population whilst lowering their medical follow-up. On the other hand, it might improve the management of the daily queue at hospitals thus allowing physicians to allocate more time to high-risk patients. Our study will propose to evaluate these different dimensions and also to investigate adherence of patients and physicians.

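### The planned bootstrap 95% CI for the ICER has no provision for resamples that cross zero QALYs, which is likely in low-risk patients and leaves that interval without cost-effectiveness meaning

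*Protocol article*

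**What the plan says.** Outcome measures defines the ICER as the difference in mean two-year cost divided by the difference in mean QALYs (from the EQ-5D) and lists it first among the secondary outcomes. It adds: "One ICER will be estimated for both the low and high risk patient groups". I read this as one ratio for each KTFS group.

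Data analysis then fixes the inference: "95% confidence intervals for ICER of eHealth versus at-hospital follow-up programs will be estimated using non-parametric bootstrapping". The type of bootstrap interval is not named, and nothing is said about a denominator near zero. The next sentence adds a second analysis: "Results of the cost-effectiveness will also be analyzed using acceptability curves", plotted against willingness to pay for a QALY.

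The article gives no expected QALY difference. For low-risk patients the Background aims to "decrease the number of visits at hospital for low-risk patients without reduction in quality of life or graft survival". The Discussion goes a little further: "it might increase the QoL of low-risk patients by offering them living conditions closer to those of the general healthy population".

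**The concern.** A ratio orders results sensibly only while its denominator keeps one sign. If resamples fall on both sides of zero QALYs:

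- a negative ratio can mean cheaper and better, or dearer and worse;
- a positive ratio can mean dearer and better, or cheaper and worse.

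The 2.5th and 97.5th percentiles of that mixture do not bound anything a decision-maker can use, and the ratio jumps between very large positive and very large negative values as the denominator passes through zero. More resamples do not cure this.

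The low-risk comparison is the most exposed. Its intended benefit is mainly on the cost side with health preserved, and it uses only part of a trial of about 250 patients. The Background expects the program to be cost-effective in both risk groups, so this interval would be read with attention, and it could be misread.

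**Working it through.** **The plan's own figures.** None concerns the ICER. The related figures in Sample size reproduce:

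- N per group = (1.645 + 0.842)² × 2 × 0.9 × 0.1 / 0.03² ≈ 1,237 (stated 1,237).
- Power with 125 per group = Φ(0.03/√(0.18/125) − 1.645) = Φ(−0.854) = 19.6% (stated 20%).

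**Assumed inputs, not in the documents.** 60 or 94 low-risk patients per arm (48% or 75% of 125); SD of 2-year QALYs 0.3; true cost difference −1000 euro; cost SD 6000; cost and QALYs uncorrelated.

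**Step 1: standard errors.** SE = SD × √(2/n).

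- n = 60: 0.0548 QALY and 1,095 euro.
- n = 94: 0.0438 QALY and 875 euro.

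**Step 2: how often the QALY interval includes zero.** With d the true gain, P = Φ(1.96 − d/SE) − Φ(−1.96 − d/SE). Over the wider range of 40 to 90 per arm and SD 0.2 to 0.4:

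| True QALY gain | P(95% CI includes 0) |
|---|---|
| 0 | 95% |
| 0.02 | 90–94% |
| 0.05 | 61–91% |
| 0.10 | 8–80% |

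**Step 3: the ratio.** Percentiles of cost difference over QALY difference, from 2,000,000 normal draws centred on the true values. Beside them is the 95% interval for net benefit at an illustrative 20,000 per QALY: 20,000·d + 1000 ± 1.96 × √[(20,000 × SE of QALYs)² + (SE of cost)²].

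| n per arm | True gain | Ratio, 2.5 to 97.5 percentile | Cheaper/better, cheaper/worse, dearer/better, dearer/worse | Net benefit interval |
|---|---|---|---|---|
| 60 | 0 | −357,000 to 353,000 | 41, 41, 9, 9% | −2,036 to 4,036 |
| 60 | 0.05 | −245,000 to 218,000 | 67, 15, 15, 3% | −1,036 to 5,036 |
| 94 | 0 | −409,000 to 407,000 | 44, 44, 6, 6% | −1,426 to 3,426 |
| 94 | 0.05 | −231,000 to 191,000 | 76, 11, 11, 2% | −426 to 4,426 |

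**Step 4: what one trial's bootstrap would show.** A real bootstrap is centred on the observed difference, so it is less evenly split than Step 3. At a true difference of zero, the share of resamples above zero is approximately uniform across trials. About 95% of trials therefore have more than 2.5% of resamples on each side, and the minority sign averages 25%. Resampling simulated trials (40 to 90 per arm, QALY SD 0.2 to 0.4, cost SD 3000) agrees: 94–97% of trials and 24–26% of resamples, with a median interval width of about 240,000 to 690,000 per QALY. With cost SD 6000 and QALY SD 0.3, a normal approximation to each trial's bootstrap gives median widths of about 530,000 (n = 60) and 580,000 (n = 94). At a true gain of 0.05 the widths are about 450,000 and 390,000, and 85% and 79% of trials still straddle zero.

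**Step 5: the alternative.** At a true QALY difference of zero (60 per arm, QALY SD 0.3, cost SD 3000), a bootstrap 95% CI for net benefit covered the truth in 93.5%, 94.8% and 95.7% of trials at willingness to pay of 0, 20,000 and 50,000.

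**The case against.** Five points can be made in the plan's defence.

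- **The trial's own hypothesis is a zero QALY difference.** A reader might infer this, but the article does not say it. The Background excludes a reduction, which means zero or better, and the Discussion allows a gain. The 90% versus 90% assumption in Sample size concerns the composite primary outcome in all patients, not QALYs in the low-risk group. This stands against the stronger reading. It does not remove the problem, because gains of 0.02 to 0.05 behave nearly as zero does at these sizes. A gain of 0.10 might escape it (8–80% chance of including zero).
- **The trial could not say whether eHealth is cost-effective.** A reader might infer this too, and it would be wrong. The acceptability curves, built from net benefit in the usual way, remain valid at a QALY difference of zero and answer that question. They are planned beside the ICER interval, however, and do not repair it.
- **The 44/44 split is not typical.** Correct. It comes from draws centred on exactly zero; the average minority share in a trial's own bootstrap is about 25%.
- **The bootstrap variant and quadrant handling belong in the SAP.** Partly fair: the article does not say that raw ratios will be ranked. But it does fix a confidence interval for the ratio itself, and the usual variants work on the same discontinuous quantity.
- **The argument is made for low-risk patients only.** For high-risk patients the Background allows improved graft survival, so the denominator may lie further from zero. No figure is given, and the same interval is planned there.

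**Conclusion.** The point holds for the ICER confidence interval and no further. With low-risk groups of 60 to 94 per arm and true gains of 0 to 0.05 QALY, the ratio limits lie at roughly ±190,000 to ±410,000 per QALY, with substantial shares of replicates on both sides of zero. Such an interval has no cost-effectiveness meaning. The widths rest on assumed group sizes, SDs and costs. The loss of ordering rests only on a QALY difference that is small relative to its standard error, which the stated aim for low-risk patients makes likely but not certain.

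This is a secondary outcome. The non-inferiority conclusion is unaffected, and the cost-effectiveness analysis as a whole stays interpretable through the planned curves. It should be corrected before analysis, but it does not threaten the trial.

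**What to change.** For each KTFS group, from the same bootstrap replicates:

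1. Report incremental net monetary benefit (willingness to pay × QALY difference − cost difference) with a 95% CI at willingness-to-pay values stated in advance, beside the planned acceptability curve, which should be built from net benefit.
2. Show the joint cloud of cost and QALY differences, with separate 95% CIs for each.
3. Give a CI for the ICER only when the 95% CI of the QALY difference excludes zero. The denominator then keeps essentially one sign and the ranking has a meaning.

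This changes analysis wording only. It needs no new data, no further resampling and no design change. The one cost is having to name the willingness-to-pay values beforehand; the article gives none, so the choice is the sponsor's.

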### Ethical approval and registration

The study is registered with the Clinical Trials Registry (NCT01615900) and has approval from the ethical Committee for Persons’ Protection (CPP, Tours, 2011-R30).

### Schedule

After initial refinement, in particular the resolution of technical issues related to the video conferencing by choosing a tablet computer, only the Nantes University hospital began the study with an inclusion of 38 patients. Patient inclusions from the other centers are possible from September 2014. Based on the yearly number of transplantations performed among the three participating centers, we expect to include 250 patients by September 2016. In line with the two-year follow up, the end of data collection is anticipated by September 2018, and publication of the results in 2019.

## Discussion

The cost-effectiveness of renal transplantation for ESRD patients is well-established compared to long-term dialysis [16–18]. Nevertheless, because the follow-up of the kidney transplant recipient is often performed at hospitals several times per year, is often coupled with significant travel requirements, long queue times and the stress associated with medical examinations, this places a measureable increase in costs and may impact the recipient’s QoL. This issue is even more pertinent when considering the increased prevalence of patients living with a functional kidney; 31,000 French patients in 2011 [1]. We hypothesized that video conferencing at home by using USB device and tablet computer may improve the efficiency of kidney transplant recipient follow-up. Such web- or mobile-based communication systems have already been considered as possible improvements for medical follow-up for other diseases; for instance in diabetes patients [19], in women after gynecological surgery [20], or for patients with chronic obstructive pulmonary disease [21].

One very important and relevant potential benefit of our adaptation of the video conferencing frequency is in regard to the frailty of patients, i.e. their risk of graft failure evaluated by the KTFS [6]. The aim of the TELEGRAFT study is to determine whether video conferencing could be used to individualize patients’ care so as to lighten (reinforce) follow-up in low (high) risk patients as compared to standard of care at hospital. This reallocation of health care resources could be profitable in many aspects. On one hand, it might increase the QoL of low-risk patients by offering them living conditions closer to those of the general healthy population whilst lowering their medical follow-up. On the other hand, it might improve the management of the daily queue at hospitals thus allowing physicians to allocate more time to high-risk patients. Our study will propose to evaluate these different dimensions and also to investigate adherence of patients and physicians.

Even if the randomized study we propose suffers from a small statistical power, the analysis will be based on a control group, i.e. comparable patients following standard of care. This design allows etiologic results without confounders, as requested by the Committee on Evaluating Clinical Applications of Telemedicine [22], in contrast to the majority of the literature in Telemedicine which is based on observational studies [23–25]. This may explain why the possible contribution of telemedicine in the improvement of medical follow-up is currently not clear [26, 27].

In conclusion, the current study allows to scientifically evaluate the etiologic impact of a novel eHealth program for the medical follow-up of kidney transplant recipients. We believe that the results will have an important impact in the transplantation community. Additionally, because the medical care of people with chronic disease is under the spotlight given the growing prevalence of such conditions in ageing populations, the proposed randomized design with 4 different sub-groups can be interesting to evaluate other personalized medicine programs.

## Abbreviations

KTR: Kidney transplant recipient
KTFS: Kidney transplant failure score
ESRD: End stage renal disease
HAS: French health authority
KDIGO: Kidney disease improving global outcomes
ERBP: European renal best practice
ROC: Receiver operating characteristic
CMV: CytoMegaloVirus
BKV: BK virus
CC: Complete check-up
HIV: Human immunodeficiency virus
EBV: Epstein-barr virus
QoL: Quality of life
VC: Video conferencing
DIVAT: Données informatisées et validées en transplantation
ICER: Incremental cost-effectiveness ratio
CI: Confidence interval.
